### Eligibility Criteria

Students in the 9th and 10th grades between the ages of 14 and 18 years were eligible to participate if they met at least one of two eligibility criteria: (1) had ever witnessed a serious injury or homicide or (2) had a girlfriend, boyfriend, or partner before or during the study consent process (prior or current experience with a romantic relationship). In addition, a student would be considered ineligible if a sibling or step-sibling had already enrolled in the study to avoid contaminating participants in different conditions.

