#### Screening

Study sites administered a grade-wide or school-wide screening questionnaire to assess adolescents’ exposure to violence and relationship status (two of the eligibility criteria noted above). For screening, sites used a variety of customized approaches based on their school protocols. All of the sites opted to include additional items on their screening questionnaires to learn more about the general health and well-being of 9^th^ or 10^th^ grade students (eg, “Do you have a primary doctor?” or “Do you eat fruits and vegetables daily?”).

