#### Consent and Assent Process

Per California law, we sought active parental consent for study participation through either a signed copy of the consent form or verbal confirmation via telephone calls (by research staff) when there was a parent signature, but the permission checkmark was ambiguous. Consent forms were available in both English and Spanish. The consent process began in one of two ways: (1) either an in-class presentation about the study was delivered by an SBHC representative or (2) students who met the screening criteria were sent invitations through a required class at school to attend an informational event, where, if interested, they received more information about the study, and parental consent forms were distributed. A single high school differed from other sites in that it provided consent forms to students ahead of the screening procedure. Students were informed that they would receive a US $10 incentive for returning a parental consent form regardless of their parent's decision. They were directed to return parental consent forms to their respective SBHC.

For students whose parents provided study consent and met the screening criteria, site liaisons compiled an eligibility log with the following data: student’s last name, first name, and middle initial; student ID (optional); student’s sex assigned at birth; student’s reported gender identity; the number of screening criteria met (selected from a dropdown menu); school (selected from a dropdown menu); agency (selected from a dropdown menu); whether students have a sibling or step-sibling at the school; and whether that sibling participated in About Us in the past (criterion for exclusion). Evaluation data collectors (EDCs) used this log onsite to determine which students were fully eligible for the assent process.

The study’s EDCs administered the study assent process on the day of the baseline survey administration at a given site. At the time of assent, prospective participants of consenting parents who met all the other eligibility criteria and agreed to study participation were enrolled in the study.

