### Randomization

Following baseline survey completion, eligible adolescents who had already received parental consent and assented to study participation were randomized to either the intervention or control group.

To assign participants to study groups (intervention or control), we used a stratified permuted block randomization procedure to ensure balance in key covariates and experience factors across intervention conditions given our need to randomize in smaller cohorts within schools by semester (ie, blocks). Specifically, eligible and consented adolescents were subdivided into strata defined by the sex assigned at birth (male or female) and whether they had one or two of the screening experience factors, followed by permuted block randomization for each stratum. Within each stratum, participants were assigned to either the intervention or control group using a 60/40 split. The goal was to create a balance of sex assigned at birth and experience factors to ensure that the intervention and control groups had an equal distribution of these factors that may affect our primary outcome of interest (ie, having vaginal or anal sex without condoms). In other words, the stratification was done to avoid the potential imbalances or confounding due to the sex assigned at birth and the number of baseline experience factors.

Students randomized to the control group received business as usual (BAU) care only. Students assigned to the control group received no special services beyond BAU provided through the schools. To measure the control group experience, we included a set of general exposure items on the impact survey to assess self-reported dosage from or exposure to teen pregnancy programming or sex education during the study period in the school and community (eg, have you had a guest speaker come to your school to provide any of the following information: abstinence information, sexuality information, pregnancy prevention information, STI or HIV information, etc). We also collected data from our schools (on a “needs and resources assessment”) to evaluate content from BAU education during the study period using a brief, web-based survey collected from our site liaisons and the schools’ health education teachers.

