**Constructed measure:**
Construct a single, dichotomous outcome coded as 1 if the respondent indicated they had vaginal or anal sex without a condom in the past 3 months, 0 if they did not, or missing otherwise.To be recoded into a single dichotomous variable (vaginal or anal sex) with response options as follows: 0=all of the time (1), as well as participants who reported not having vaginal or anal sex in the past 3 months; 1=some (2) or none of the time (3); and (?)=missing response for vaginal or anal sex without a condom in the past 3 months.**Timing of measure:** 9 months following the completion of the program.

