### Data Cleaning

#### Phase I

Data cleaning is being implemented in three phases. At the baseline, 3-month, and 9-month surveys, the evaluation team engages in a screening process beginning during data entry and using built-in checks for participant entries via Qualtrics. We are using predefined expectations about normal ranges (eg, aged 14 to 18 years), flagging of dubious data entry and patterns (eg, using prompts to confirm an entry), and skip patterns (eg, if students reported having been in a relationship, they received an additional branch of questions not given to those who never were in a relationship).

After retrieving Qualtrics data from each participant survey from the EDCs, project staff transfers the files to a password-protected shared drive. Participant data are transferred and warehoused in SPSS (version 27; IBM) by data wave (ie, baseline, 3 months, and 9 months). Using SPSS, we are recoding variables, creating new variables (eg, check-all variables, such as race and sexuality, recoded into one categorical variable), and labeling and formatting variables for analysis.

For each data wave and merged data sets, data are checked to ensure they meet predefined range expectations, logical skip patterns, and consistency checks and missing data patterns by examining variable descriptive summary statistics (eg, minimum, maximum, mean, median, and SD), frequency distributions, cross-tabulations, and graphical explorations of variable distributions (eg, box plots, histograms, and scatter plots). Data are also checked against expected data collections (based on the number of randomized participants, lags between baseline, and follow-up surveys) and errors in transferring data from Qualtrics (eg, duplicate entries and inadvertent deletions). This process is implemented using SPSS and SAS (version 9.4; SAS Institute).

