### Statistical Analysis Models

For dichotomous outcomes at 9 months, we will use logistic regression models with covariates (see Textbox 2) for the intervention, baseline outcome variables, strata variables (sex assigned at birth and number of screening experience factors present), sociodemographic characteristics (age and race and ethnicity), the time elapsed between baseline and the follow-up survey (at 3-month and 9-month follow-up), cohort, and school. For continuous outcomes, we will use linear regression models with covariates for the intervention, baseline outcome variables, strata variables (sex and number of screening risk factors present), sociodemographic characteristics (age and race and ethnicity), the time elapsed between baseline and follow-up surveys (at 3-month and 9-month follow-up), cohort, and school. Additional (exploratory) analyses will test for 3-way and 2-way statistical interactions and adjust for prognostic factors such as potential confounders of intervention effects. Similarly, we will include a covariate that captures whether our outcome data were collected pre-COVID-19 versus during the COVID-19 pandemic. Potential 2-way interactions involving this covariate and intervention group, age and grade, and relationship status will be examined to test the differential effects of the pandemic on outcomes of interest.

Covariates included in impact analyses.**Screening factor:** one or two screening factors present (categorical variable).**Age (years):** baseline date to DOB (continuous variable).**Sex:** sex assigned at birth; 1=male, 2=female (dichotomous variable).**Race and ethnicity:** White, Black, Hispanic, other (categorical variable).**Number of days between baseline and the follow-up survey (3 or 9 months):** follow-up date to baseline date (continuous variable).**Cohort:** cohort 1 (spring 2018), cohort 2 (fall 2018), cohort 3 (spring 2019), cohort 4 (fall 2019), and cohort 5 (spring 2020; categorical variable).**School:** high schools 1 to 7.

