### Handling Missing Data

Our general approach to missing data will involve taking advantage of all observed information while not exaggerating the precision of findings based on incomplete data [41,42].

All variables described for our final regression models will be used in our imputation procedures. That is, outcome measures (at 3-month and 9-month follow-up analyzed separately), treatment condition, baseline outcome variables, strata variables (sex and number of screening experience factors present), sociodemographic characteristics (age, race, and ethnicity), the time elapsed between baseline and follow-up survey (at 3-month or 9-month follow-up), and school. The treatment and control group participant data will be imputed separately [43].

Multivariate imputation by chained equations [44] methods using PROC MI and MIANALYZE procedures in SAS will be used to create multiple imputations (replacement values) for multivariate missing data (eg, continuous, binary, unordered categorical, and ordered categorical data) based on a fully conditional specification [45], where each incomplete variable is imputed by a separate model [46]. All missingness (nonresponse, program attrition, or study loss to follow-up) will be treated the same way for our benchmark analysis. Additional analyses (see Sensitivity Analysis) will be explored where reasons for program attrition are accounted for in the generation of imputed covariate and outcome values. All variables (ie, outcome and baseline characteristics) described in the above analysis models will be used for the imputation procedures. The number of data sets to be imputed will be determined using the quadratic rule recommended by von Hippel [47]. In addition to the baseline value of the outcome of interest, age, race and ethnicity, the sex assigned at birth, and the number of screening experience factors (1 or 2; ie, adolescents had either exposure to violence or a prior or current experience with a romantic relationship or both), and time (days) between baseline and 3-month or 9-month follow-up will be included in our final analysis models (ie, linear and logistic regression).

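### Screening history enters the primary and imputation models only as a count, and baseline behaviour as a yes/no that merges inactive students with consistent condom users: precision is lost, validity is not

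*Protocol article*

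**What the plan says.** All references are to the protocol article.

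- **Eligibility Criteria.** A student qualifies on at least one of two different experiences: "1) had ever witnessed a serious injury or homicide or (2) had a girlfriend, boyfriend, or partner before or during the study consent process".
- **Randomization.** Strata are sex assigned at birth and "whether they had one or two of the screening experience factors".
- **Statistical Analysis Models, Textbox 2.** The screening covariate is the same count: "one or two screening factors present (categorical variable". The other listed covariates are age, sex, race and ethnicity, days to follow-up, cohort and school. The text of that section adds baseline outcome variables, in the plural; Textbox 2 lists none.
- **Handling Missing Data.** The count is explained as "adolescents had either exposure to violence or a prior or current experience with a romantic relationship or both". The final model takes the baseline value of the outcome being analysed, in the singular. The imputation uses the regression variables and is run separately by arm.
- **Measures, Textbox 1.** The zero category of the primary outcome is "0=all of the time (1), as well as participants who reported not having vaginal or anal sex in the past 3 months".
- **What is collected.** Sites used a "screening questionnaire to assess adolescents’ exposure to violence and relationship status". The eligibility log passes on only "the number of screening criteria met (selected from a dropdown menu". The survey itself asks about relationships: "if students reported having been in a relationship, they received an additional branch of questions not given to those who never were in a relationship". Recent abstinence is a secondary outcome, and Assessment of Baseline Equivalence compares secondary outcomes between arms at baseline.
- **Other routes to adjustment.** Statistical Analysis Models allows prognostic adjustment as exploratory work. Assessment of Baseline Equivalence adds a baseline measure to the outcome models if the arms differ significantly on it.

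**The concern.** A student who has witnessed violence but never had a partner and a student who has had a partner but witnessed no violence share one covariate level. The article's Background and Rationale links romantic relationships to greater odds of intercourse and describes them as the setting of most sexual interactions. The two groups can therefore be expected to differ in risk of condomless sex, and the count cannot separate them.

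The baseline outcome has the same limitation. A student with no sex in the past 3 months and a student who had sex with a condom every time are both coded 0, although the second is already sexually active.

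At stake is precision for the primary comparison after recruitment has ended short of target. A second consequence concerns the benchmark analysis, which imputes every missing outcome from the same variables. If relationship history or recent sexual activity predicts both the outcome and dropout, leaving it out makes the missing-at-random assumption harder to defend.

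**Working it through.** **1. The plan's own sample size.** Inputs from Power Analyses: difference 0.09, prevalence ratio 0.74, allocation 3:2, two-sided 5%, power 80%.

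- Control prevalence: 0.09 / (1 − 0.74) = 0.346. Intervention prevalence: 0.74 × 0.346 = 0.256. The implied odds ratio is 0.650, as stated.
- n(control) = [1.96·√(p̄q̄(1 + 1/r)) + 0.842·√(p_c q_c + p_t q_t / r)]² / 0.09², with r = 1.5 and p̄ = (0.346 + 1.5 × 0.256)/2.5 = 0.292. This gives 337 control and 506 intervention. With 0.35 v 0.26 it gives 339 and 509. The stated 339 and 508 are reproduced.

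**2. Power at the size achieved.** Planned total: 508 + 339 = 847. Randomised: 316 + 217 = 533, or 533/847 = 63%. The same unadjusted test has power 0.61 at 316/217. At 237/163 (400 analysed, 75% retention, an assumption) it is 0.49.

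**3. What finer covariates add.** The documents give no predictor strengths, so these are assumed. Logistic models were simulated with 3,000 replicates per scenario, holding the marginal prevalences at 34.6% v 25.6%. The share with both factors was 30%. The violence-only share was 10% or 30%, and the rest were relationship-only. Assumed baseline behaviour (no recent sex / always condom / condomless) was 95/2.5/2.5% for violence-only, 72/10/18% for relationship-only and 66/11/23% for both. Assumed log odds for the 9-month outcome:

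| Strength | Violence only v relationship only | Both v relationship only | Always condom v no recent sex | Condomless v no recent sex |
|---|---|---|---|---|
| Weak | −0.3 | 0.2 | 0.7 | 1.0 |
| Moderate | −1.0 | 0.3 | 1.2 | 2.0 |
| Strong | −2.0 | 0.3 | 2.0 | 3.0 |

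The plan model has treatment, the one/two count and the binary baseline outcome. The extended model splits factor type and baseline behaviour into three levels each. Age, race and ethnicity, school, cohort, elapsed time and missing data were not simulated.

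| Analysed | Violence only | Strength | Power, plan | Power, extended | Gain (points) | Equivalent N gain |
|---|---|---|---|---|---|---|
| 533 | 10% | Weak | 0.626 | 0.634 | 0.8 | 1.2% |
| 533 | 10% | Moderate | 0.669 | 0.688 | 1.9 | 3.6% |
| 533 | 10% | Strong | 0.732 | 0.776 | 4.4 | 11.8% |
| 533 | 30% | Weak | 0.629 | 0.635 | 0.6 | 1.1% |
| 533 | 30% | Moderate | 0.666 | 0.689 | 2.3 | 5.1% |
| 533 | 30% | Strong | 0.740 | 0.803 | 6.3 | 16.8% |
| 400 | 10% | Weak | 0.498 | 0.507 | 0.9 | 1.3% |
| 400 | 10% | Moderate | 0.561 | 0.581 | 2.0 | 3.8% |
| 400 | 10% | Strong | 0.608 | 0.663 | 5.5 | 11.5% |
| 400 | 30% | Weak | 0.504 | 0.507 | 0.3 | 0.9% |
| 400 | 30% | Moderate | 0.565 | 0.586 | 2.1 | 4.8% |
| 400 | 30% | Strong | 0.601 | 0.672 | 7.1 | 15.6% |

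**4. Can factor type be recovered?** The log carries the count only, but count plus survey relationship history is enough. One factor and never partnered is violence only; one factor and ever partnered is relationship only; two factors is both. No baseline violence item is needed. The derivation fails only where screening and survey answers disagree.

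**The case against.** The strongest reply is that nothing here is invalid. The model adjusts for exactly the strata used in randomisation, plus the baseline outcome and other covariates, and that is standard. This stands: a reader might infer that the poolings bias the treatment effect, but randomisation protects the comparison whichever prognostic covariates are included.

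Second, a reader might infer that strong predictors have been left out. The documents support the direction only. The relationship criterion covers any past or current partner, which may predict behaviour in a 3-month window less well than current status. The violence-only share is not reported and may be small. This also stands.

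Third, a reader might size the gain by dividing the sample by one minus the added explained variance. With 5% to 10% assumed, that gives 533/0.95 = 561 to 533/0.90 = 592, and power from 0.60 (unpooled variance) to 0.62–0.65. That calculation is not sound here. It starts from unadjusted power although the plan already adjusts, and it applies linear-model reasoning to a logistic model, where the gain comes from a larger conditional effect rather than a smaller standard error.

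Fourth, the article partly provides for this. The plural baseline outcome variables could be read to include abstinence, and the exploratory and imbalance-triggered adjustments could bring these variables in. This does not answer the point. The missing-data section is singular, exploratory analyses do not change the benchmark, and a significance trigger selects on chance imbalance rather than prognosis.

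Finally, the article attributes losses to school closures, poor contact details and transfers. Nothing in it links missingness to these variables, so the imputation benefit is plausible but not shown.

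**Conclusion.** The point holds as one of efficiency. The prespecified primary and imputation models use a coarser version of baseline information than the trial collects, and no other stated analysis brings the finer version into the benchmark.

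Relative to the plan's own adjusted model, the loss is about 0 to 1 power point if the predictors are weak, about 2 if moderate and about 4 to 7 if strong. That equals roughly 1%, 4% to 5% and 12% to 17% of sample size. These figures rest entirely on the assumed strengths, group shares and baseline behaviour; the 400-student case also assumes 75% retention. The improvement is worth making because recruitment is over and it costs almost nothing, but it does not restore the planned 80% power except at the most favourable assumption tried.

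**What to change.** Before outcomes are seen by arm, amend the 9-month primary model and its imputation model as follows.

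- Keep the one/two-factor randomisation stratum.
- Add baseline vaginal or anal sex in the past 3 months (yes/no). With the existing baseline outcome this gives three levels: no recent sex, always protected, condomless.
- Add baseline relationship history. With the count this separates violence only, relationship only and both. State how disagreements between screening and survey are resolved.
- State which baseline outcomes the benchmark model contains, and make Textbox 2, Statistical Analysis Models and Handling Missing Data agree.

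The cost is about two degrees of freedom on a model with roughly 19 terms (school 6, cohort 4, race and ethnicity 3, and one each for treatment, baseline outcome, sex, factor count, age and elapsed time). No new data are collected. Because imputation is run by arm, the violence-only cell may be small: at a 10% share, 217 × 0.10 is about 22 controls. If that makes the model unstable, the sexual-activity covariate should take priority and relationship history can be dropped by a rule fixed in advance.

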#### Presentation of Continuous Outcomes

Least squares (LS) means, corresponding SEs, 95% 2-sided CIs, and 2-tailed *P* values will be presented for the within-group (ie, intervention and control) outcome measures. For each between-group, the difference in LS means, corresponding SE, 2-sided 95% CI, and 2-tailed *P* value will also be derived from the linear regression model and presented. Standard model diagnostics will be performed to assess the validity of the proposed model. These diagnostics will include examining the residuals for normality and homoscedasticity as well as testing for the significance of the intervention by baseline outcome interaction terms.

#### Presentation of Categorical Outcomes

The estimated odds ratio, SE, 95% Wald CI, and *P* value will be presented for each between-group comparison of interest. Standard model diagnostics will be performed to assess the validity of the proposed model. These diagnostics will include testing the goodness of fit with the Hosmer-Lemeshow test and examining influence statistics for potentially outlying observations. In addition, the number and percentage of subjects with a primary outcome (eg, condomless vaginal or anal sex) will be presented for each treatment group, including model estimated probabilities and statistical significance of differences observed (at α=.05).

